## Abstract

**Background:**

Buruli ulcer (BU) can lead to disfiguring ulcers and permanent disability. The 2030 World Health Organization (WHO) road map for Neglected Tropical Diseases (NTDs) calls for major scaling up in diagnosis and management to eliminate disability due to the disease. Current treatment for BU is with daily oral rifampicin (10mg/kg dose) and clarithromycin (15mg/kg dose) for eight weeks, combined with standard gauze wound dressings. Dialkylcarbamoyl chloride (DACC)-coated dressings have been shown to irreversibly bind bacteria on wound surfaces resulting in their removal when dressings are changed.  This trial aims to determine whether combining a high-dose oral rifampicin regimen with DACC dressings can improve the rate of wound healing relative to standard-dose oral rifampicin combined with DACC dressings.

**Methods:**

This is an individual, multi-centre Phase 3 randomised controlled trial, which will be conducted in three clinical sites in Ghana. The primary outcome measure will be the mean time to clearance of viable mycobacteria. Cost and health-related quality of life data will be collected, and a cost-effectiveness analysis will be performed.

**Discussion:**

The findings from this trial could lead to a change in how BU is treated. A shorter but more efficacious regimen would lead to improved treatment outcomes and potentially substantial financial and economic savings.

## Introduction

Buruli ulcer (BU), a neglected tropical disease (NTD) caused by infection with *Mycobacterium ulcerans* (MU), occurs in more than 30 countries worldwide with a focus in rural West Africa^1^. In Ghana, the disease is confined to the south, and in particular parts of the Ashanti Region^2^. Access to treatment in rural areas can be challenging and late presentation is typical, due to fear, stigma, suspicion about conventional medicine and high cost of care-seeking for affected individuals and their families^3,4^. The mode of transmission remains unknown; however, children aged five to 15 years are most commonly affected^5^. Initially, the disease manifests as either a subcutaneous painless nodule tethered to the skin or an intradermal plaque. These initial manifestations enlarge over a period of days to weeks, ulcerating in the centre and causing large disfiguring skin ulcers which can sometimes affect the bone, causing permanent disfigurement and long-term disability. Even with effective antimicrobial therapy, BU wound healing is slow, often requiring many months of care^6^. Studies from Ghana and Nigeria have reported that BU imposes substantial costs on affected individuals, their households^7,8^, and the health system^9^.

Clinical trials in Ghana led the World Health Organization (WHO) to recommend that BU be treated with daily oral rifampicin (10mg/kg dose) and clarithromycin (15mg/kg dose) for eight weeks^6^. Previous studies have shown that by week 4 of treatment almost 50% of patients have either healed or live MU can no longer be detected by a combined 16S rRNA and qPCR for IS2404. These data highlight that in some patients a short course of antibiotics may be effective^10^. Preliminary data from Ghana suggests two major factors contribute to variability in healing: the baseline bacterial load and the occurrence of paradoxical reactions^11^. An additional factor in the variability of healing rates is the possible role of secondary infections of BU wounds. It has been proposed that mycolactone, a toxin produced by MU, may limit occurrence of secondary infections in BU lesions, but supporting evidence is sparse. Several studies conducted in Ghana reported diverse microbial communities being isolated within BU lesions. It remains unclear whether these other bacteria represent true co-infections, secondary colonisation, or opportunistic commensals^12,13^. Clinicians sometimes prescribe additional antibiotics to treat potential secondary infections, even though it is unclear whether additional antibiotics are necessary. Such prescribing practices may contribute to antimicrobial resistance (AMR), highlighting the need to understand if and how these isolates interfere with disease resolution^12^.

Wound dressings with antimicrobial properties may help to improve outcomes in patients with BU. Dialkylcarbamoyl chloride (DACC)-coated dressings irreversibly bind bacteria on wound surfaces resulting in their removal when dressings are changed^14–16^. They represent an innovative approach to prevention of secondary infection without use of antimicrobials. A systematic review of seventeen studies, including 3,408 patients with chronic wounds, used silver-impregnated dressings as an active comparator^17^. A single randomised controlled trial (RCT) and two cohort studies demonstrated that DACC-coated dressings reduced bacterial load to a greater extent than silver-impregnated dressings and one RCT demonstrated a positive effect on wound size reduction^14,17,18^.

Higher doses of appropriate antimicrobials may also further improve outcomes in patients with BU. The 10mg/kg dose of rifampicin, which WHO recommends for BU treatment, was selected because it is the dose used in tuberculosis treatment. Multiple tuberculosis studies have demonstrated that higher-dose rifampicin is safe and well tolerated^19,20^ and comparative trials of its efficacy for tuberculosis are underway^19,21,22^. Preliminary data for BU suggest that higher-dose rifampicin may improve outcomes and may facilitate shortening of regimens in part because it may clear viable MU more quickly^23^. Collectively, these data suggest that high-dose rifampicin is safe and may be an efficacious strategy to improve outcomes for individuals with BU; however, its use has not been evaluated in a clinical trial.

To inform decisions about whether to include DACC dressings and high-dose rifampicin in revised BU treatment guidelines, policy makers require evidence on safety and efficacy, as well as costs and cost-effectiveness. An individual DACC dressing or high dose of rifampicin is more expensive than a standard dressing or rifampicin dose. Investing in these novel interventions may, however, generate cost-savings for households and the health service if they are successful in decreasing time to wound healing, the number of treatment visits, and long-term disability. It is therefore unclear whether DACC dressings and high-dose rifampicin would cost more or less overall than standard treatment. If they prove more expensive, policy makers will want to consider whether the additional costs are worth the health improvements, taking into account the many potential alternative uses of limited resources for healthcare in Ghana. While previous studies have assessed the economic burden of BU treatment on affected individuals^7,8,24^ and the health system^9,25^, no analyses have compared the cost-effectiveness of alternative BU treatment regimens.

To address these research gaps, we designed an RCT to investigate whether combining high-dose rifampicin and DACC dressings may significantly improve the time to clearance of viable mycobacteria from wounds, reduce paradoxical reactions and secondary infections, and result in improved outcomes for individuals with BU, as compared with standard-dose rifampicin and DACC dressings. Alongside this trial, we will also conduct a full economic evaluation, in which we will compare the financial and economic costs and outcomes of these two BU treatment strategies from a societal perspective. We will model incremental costs and cost-effectiveness of these strategies relative to one another and to standard care, and explore equity implications of adopting a new strategy.

## Methods

This manuscript has been prepared according to the Standard Protocol Items: Recommendations for Interventional Trials^26,27^ (SPIRIT) statement (Additional file 1, *Extended data*^28^). We report here Protocol version 1.0 dated 23 March 2021.

### Trial design

This is an individually randomised multi-centre trial of high-dose rifampicin and DACC dressing, compared to standard-dose rifampicin and DACC dressings. Participants enrolled in the study will be allocated 1:1 to one of the two treatment groups and followed up until 12 months from the point of randomisation. Consent and baseline data collection will precede randomisation. A summary of the study pathway is shown in Table 1.

### Study setting

The trial is set in BU treatment centres within selected districts in Ghana: Ga West Municipal Hospital, Pakro Health Centre and Wassa Akropong Municipal Hospital. These districts are endemic for BU and the facilities have extensive experience in providing care for the disease.

### Eligibility criteria

Individuals aged five to 80 yearsIndividuals with a nodule, plaque or ulcer, with or without associated oedemaPositive test for MU by PCR for IS2404 (identification of MU DNA from a swab or FNA sample)Able to give informed consent (and/or assent) or responsible adult able to give informed consentAble and willing to follow the protocol requirements

### Exclusion criteria

Participating in any other interventional study at the time of randomisationKnown allergy to any component of DACC dressing materialsKnown contraindication to either rifampicin or clarithromycinPregnancy

### Interventions

#### Intervention description

Individuals who have consented to participate will be randomised to either of the two arms of intervention. In the intervention group (HR+DACC), participants will receive daily high-dose oral rifampicin (20mg/kg) and oral clarithromycin (15mg/kg) for four weeks and DACC-coated dressing applied to the wound and changed every 48 hours until the lesion heals.

The control group (SR+DACC) will receive WHO-recommended daily oral rifampicin (10mg/kg) and oral clarithromycin (15mg/kg) for eight weeks and DACC-coated dressing applied to the wound and changed every 48 hours until lesion heals.

#### Criteria for discontinuing or modifying allocated interventions

In the event that a participant becomes pregnant after starting the study medication, she will be withdrawn and followed up by an obstetrician throughout the pregnancy to assess any effect on the pregnancy outcome. If a live baby results, then the baby will be followed up by a paediatrician for two years.

Participants on anti-hypertensive drugs will have their blood pressure closely monitored to allow for appropriate decision-making. As part of the trial team, an experienced physician will be available to make decisions regarding treatment, which may include adjustment to doses of antihypertensives if need be.

#### Strategies to improve adherence to interventions

Community-based surveillance volunteers (CBSVs) within the study districts will be used to support patient follow-up and adherence to trial medications and dressings. Transportation cost of participants to travel between their homes and the health facilities will be reimbursed.

#### Relevant concomitant care permitted or prohibited during intervention period

All concomitant medication taken by the participant during the study will be monitored and recorded in the Case Report Form (CRF) with trade name and generic name, route or formulation, dosing scheme, the indication, and start and stop dates of administration.

### Outcomes

#### Primary outcome

The primary outcome measure is the mean time to clearance of viable MU.

#### Secondary outcomes

The following secondary outcomes will be assessed:
The proportion of participants with no viable MU organisms, as assessed by a combined 16s rRNA reverse transcriptase/IS2404 real-time qPCR assay, detectable at Weeks 2, 4, and 6, during antimicrobial intervention and at Week 8 after both groups have completed rifampicin and clarithromycin treatment.The proportion of participants achieving complete healing of lesions at Week 20, where complete healing is defined as re-epithelialisation of ulcerated area with stable scar formation during a three-month observation period.The proportion of participants with reoccurrence of BU in each treatment arm; indicator of reoccurrence being the appearance of a new lesion within 12 months of treatment and is not considered as a paradoxical reaction. This will be assessed by the presence of viable micro-organisms detected by culture or 16S rRNA assay after completion of antibiotic treatment and complete healing of the initial lesion.The proportion of participants with paradoxical reaction in each arm of intervention. Paradoxical reaction is defined as:
an initial improvement in the clinical appearance of lesion upon antimicrobial treatment of BU followed by deterioration of the lesion or its surrounding tissuesor the appearance of a new lesion(s)or examination of excised tissue from the clinical lesion showing evidence of an intense inflammatory reaction consistent with a paradoxical reaction.
The proportion of participants who experience secondary infection defined as the occurrence of new purulent discharge within the BU lesion accompanied by microbiological evidence of infection by an organism other than MU.

#### Sample size

The sample size is based on existing data which demonstrated a mean time to clearance of viable MU with standard dose rifampicin and Vaseline gauze dressings (standard care) of eight weeks^10^, with a standard deviation of four weeks. Assuming a lower standard deviation of three weeks for high-dose rifampicin (intervention), 100 participants (randomised 1:1) would enable us to detect a reduction of two weeks in mean time to RNA clearance with 80% power and 5% significance. In addition, 100 participants would also allow us to see an increase of approximately 27% in the proportion of patients with healed wounds at 20 weeks in the high-dose rifampicin arm. This is based on a conservative assumption that 50% of wounds would be healed at 20 weeks with DACC dressings and the standard dose rifampicin^10^. Assuming a loss to follow-up rate of 10%, we therefore plan to recruit 112 participants to ensure that at least 100 participants are followed up for a minimum of 20 weeks.

#### Recruitment

Recruitment started in November 2021 and continues. The estimated primary study completion date is May 2024 with an enrolment capacity of five participants per month. There will be facility-based recruitment of individuals who seek treatment for BU following counselling and consent. Participants will be recruited from three hospitals in Ghana: Pakro Health Centre, Ga West Municipal Hospital and Wassa Akropong Government Hospital.

### Randomisation, allocation, and blinding

A computer-generated random allocation sequence was prepared at the London School of Hygiene & Tropical Medicine (LSHTM) using block randomisation stratified by site, BU stage (Stage I-III) and specific randomisation number placed in sealed opaque envelopes. This was done in a secure manner and access restricted to avoid any possibility of viewing the allocation sequence. Participants enrolled in the study will be allocated 1:1 to one of the two treatment groups: HR+DACC or SR+DACC. The recruiting clinician will be given randomly generated treatment allocations within sealed opaque envelopes. Once an individual has consented to participate in the trial and has satisfied all the inclusion criteria, an envelope corresponding to their study-specific stratification and number will be opened. The participant will then be offered the allocated treatment regimen with a unique study code, kept with the local site team and the study coordinators. A skilled wound assessor blinded to the allocation will evaluate wound images for assessment of healing to avoid bias and maximise validity of results. Participants at each site will be recruited by the recruiting clinician. It will not be possible to blind participants and clinical research staff administering drugs. Clinical and laboratory data will be collected by staff blinded to the study arm.

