#### Resource use and cost data

At every scheduled visit, data will be collected on costs incurred by the household that can be attributed to a householder having BU and/or seeking treatment for BU. At Week 0, all costs incurred since onset of BU symptoms will be collected. At each follow-up visit, costs related to BU since the last visit will be collected. These include costs of medicines, hospitalisation, consultation, transportation as well as opportunity costs relating to having and treating BU (for example, missed work or school). Socioeconomic data on household income, expenditure (frequent and non-frequent items) and asset ownership will also be collected at Weeks 0, 2, and 4 to establish a month of income and expenditure data based on prospective data collection with a maximum of 2 weeks’ recall. Information on how households cope with the burden of BU will also be collected at each follow-up visit.

The programme-level costs of resources used in implementing the new interventions (high-dose rifampicin and DACC dressings) are expected to include costs of training health workers, intervention planning, and implementation. These costs will be collected from the project’s activity and financial records; the value of donated items will be estimated based on market prices. Where necessary, government sources will also be consulted for relevant cost data.

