### Trial governance

The trial will be overseen by a Trial Steering Committee (TSC). The TSC will have an independent chair and members with clinical expertise. Meetings will be scheduled before enrolment and regular meetings held either by teleconference or face-to-face.

Day-to-day management of the study will be co-ordinated by a central Trial Management Group (TMG) at the Kumasi Centre for Collaborative Research (KCCR) in Tropical Medicine including the Principal Investigator, Senior Trial Clinician and Trial Coordinator and the Trial site Coordinators. This group will provide regular supervision of the trial and ensure that it is conducted in accordance with the principles of GCP and other relevant regulations.

An independent Data Monitoring Committee (DMC) has been established to provide oversight of the study. The DMC will review safety and efficacy data during the active phase of the trial. They will advise on the continued recruitment of trial participants. This committee consists of an independent chair, a statistician and members with clinical and methodological expertise. An independent clinical expert panel (separate from the DMC) has been established to provide external clinical assessment of outcomes where required, for example judging potential paradoxical reactions.

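### The protocol says clinical data are collected blind to arm, but unblinded participants and antibiotic courses of four versus eight weeks leave that blind unsecured for face-to-face data, paradoxical reaction above all

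*Protocol article*

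**What the plan says.** The section on randomisation, allocation and blinding makes three statements that bear on this point.

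- On who is unblinded: "It will not be possible to blind participants and clinical research staff administering drugs".
- On data collection: "Clinical and laboratory data will be collected by staff blinded to the study arm".
- The participant is offered the allocated regimen "with a unique study code, kept with the local site team and the study coordinators".

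The same section assigns a blinded assessor to judge healing from wound images.

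The intervention description gives the high-dose arm "daily high-dose oral rifampicin (20mg/kg) and oral clarithromycin (15mg/kg) for four weeks" and the control arm "WHO-recommended daily oral rifampicin (10mg/kg) and oral clarithromycin (15mg/kg) for eight weeks". No placebo is described.

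Under trial governance, an independent clinical panel exists "to provide external clinical assessment of outcomes where required, for example judging potential paradoxical reactions". The article does not say which cases go to the panel or whether it is masked to arm.

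**The concern.** A statement that outcome data are collected blind tells readers that arm knowledge could not influence what was recorded. Here the arms differ, for four weeks, in something the participant knows and is likely to mention: whether daily tablets are still being taken. A member of staff who learns this at one visit knows the arm at every later visit.

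Paradoxical reaction and secondary infection are at stake. Both begin with someone at the bedside deciding that something has happened. The introduction and the discussion name fewer paradoxical reactions and fewer secondary infections as hoped-for benefits of the intervention. If arm knowledge affects how readily such events are flagged, these comparisons could be biased in either direction, and a report would describe them as protected by a blind that the design had not secured.

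**Working it through.** The point rests on comparing sections of the protocol article. The only arithmetic is an illustration at the end.

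**1. When the arms look different.** Antibiotics run for 4 weeks in one arm and 8 weeks in the other (intervention description). For 8 − 4 = 4 weeks, tablet-taking identifies the arm. The Week 6 visit falls inside this window and the Week 8 visit closes it (participant timelines).

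**2. What is asked at those visits.** Table 1 schedules history and physical examination, adverse events, clinical assessment, the pain scale, functional limitations and quality of life at both Week 6 and Week 8. A history or adverse-event interview that covers the preceding two weeks will readily show whether tablets are still being taken.

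**3. How long the knowledge lasts.** After Week 8 neither arm is on antibiotics, but anyone who learnt the arm earlier still knows it. Follow-up runs to 12 months.

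**4. Exposure by outcome.**

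| Outcome | Basis in the protocol | Exposure |
|---|---|---|
| Clearance of viable organisms (primary) | 16S rRNA/IS2404 laboratory assay | Not affected by this argument |
| Healing | Blinded reading of wound images | Not affected |
| Paradoxical reaction | Mainly clinical: improvement then deterioration, or a new lesion; excised tissue is one alternative | Most exposed |
| Secondary infection | New purulent discharge plus microbiological evidence of another organism | Lesser: the laboratory part limits false positives, but the swab is taken only after a bedside finding |
| Recurrence | New lesion not considered a paradoxical reaction, with viable organisms on culture or 16S rRNA assay | Lesser: mainly through how a new lesion is classified |
| Pain, quality of life | Reported by the participant | Open-label whoever collects them, because the participant knows the arm |

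**5. Illustration of size.** The documents give no paradoxical-reaction rate and no information on differential recording, so both are assumed. The group size comes from the sample size section: 100 evaluable participants allocated 1:1, hence 100 / 2 = 50 per arm. (The recruitment target reproduces: 100 / 0.90 = 111.1, which rounds up to 112.)

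Let the true risk be p in both arms, with a fraction s of events recorded in one arm and all events recorded in the other. The observed risks are p and p × s, so the observed risk ratio is s although the true ratio is 1. Exact binomial enumeration of a two-sided pooled z-test at 5% gives these rejection rates:

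| True risk p | s = 1 | s = 0.90 | s = 0.75 | s = 0.50 |
|---|---|---|---|---|
| 10% | 5.1% | 5.3% | 6.9% | 14.5% |
| 20% | 5.2% | 6.0% | 10.6% | 30.3% |
| 30% | 5.0% | 6.3% | 13.7% | 44.3% |

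A 10% shortfall in recording hardly matters for the test. A 25% shortfall raises the false-positive rate to about 7% to 14%, and a 50% shortfall to about 15% to 44%. In every column the point estimate is wrong by the factor s, whether or not the test rejects. The planned model for binary outcomes is modified Poisson regression, so the test here is an approximation to it.

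**The case against.** The best defence is that the protocol separates staff who administer drugs from staff who collect data, and that a condensed article leaves the details of that separation to the full protocol. Several other points also favour the plan.

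- Secondary infection and recurrence both need laboratory evidence.
- Photographs and measurements at each visit leave a record that can be audited.
- The analysis is to be blind to allocation.
- Potential paradoxical reactions are the protocol's own example of what the panel judges, which fits routine referral.

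Much of this stands and limits the point. A reader might infer more than the documents support in four places:

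- **That the blind cannot hold for any clinical data.** The documents show a likely route to unblinding from Week 4 onwards. They do not show that it happens for every collector or every item.
- **That the panel sees only cases that unblinded sites choose to refer.** The text does not say who refers or on what basis. The gap is that referral is not fixed and masking of the panel is not stated.
- **That the household cost questions reveal the arm.** Follow-up cost data cover medicines ("These include costs of medicines, hospitalisation, consultation, transportation as well as opportunity costs relating to having and treating BU"), but the discussion says antimicrobial treatment is free in endemic countries, so this route is weak.
- **That recurrence is among the stated hoped-for benefits.** Neither the introduction nor the discussion names it as one.

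The defence does not remove the core of the point. The blinding sentence is a positive claim, not an omitted detail. Separating roles does not stop an unblinded participant from answering a question about the past two weeks. Laboratory confirmation cannot recover an event that was never flagged or swabbed, and a blinded analysis cannot correct what was recorded.

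**Conclusion.** The point holds in limited form. The claim of blinded collection is not secured for participant-facing clinical data and is likely to fail from Week 6, with carry-over to later visits. It can stand for laboratory work and for image-read healing, so inference on the primary outcome is not touched by this argument. Paradoxical reaction is the outcome most at risk, followed by secondary infection.

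The size and direction of any bias are unknown. The illustration assumes true risks of 10% to 30% and one-sided under-recording, neither of which comes from the documents. Modest differences would also be imprecise. With a true risk of 20% and recording of 90% and 70%, the observed risks are 0.20 × 0.90 = 18% and 0.20 × 0.70 = 14%. That is 9 versus 7 events in 50 per arm, a risk ratio of 0.78 with a 95% confidence interval of about 0.31 to 1.93. Such a result would distort the estimate but would not by itself produce a significant finding.

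The verdict assumes that no placebo is used and that no further procedure keeps collectors blind. If the full protocol contains such a procedure, or a panel charter that fixes referral and masking, stating it would largely answer the point.

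**What to change.** 1. **Blinding statement.** Limit it to laboratory staff and the wound-image assessor. Describe participant-facing clinical, adverse-event, pain and quality-of-life data as open-label, or state how the collectors are kept blind.
2. **Paradoxical reaction.** In the trial governance section, replace the discretionary wording with referral of every suspected paradoxical reaction, including every new lesion, to the existing panel. Each file should hold the photographs, measurements and laboratory results already collected, with allocation and antibiotic dates removed. Use the panel's classification as the outcome. The recurrence definition depends on completed antibiotics; that condition can be applied to the data after the panel has classified the case.
3. **Secondary infection.** Keep the microbiological definition and report its ascertainment as open-label. The panel need not review every purulent discharge.

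The cost is a protocol amendment and some file preparation. Recruitment is under way, so the amendment needs steering committee approval and notification of the sponsor, ethics committees and regulator. Someone must mask each file before the panel sees it. No extra measurement is needed: photographs and lesion measurements are scheduled at every follow-up visit, so suspected cases in participants already enrolled can be reviewed in the same way.
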